The effect size of the primary endpoint is the relative risk of contracting SSI for the intervention group versus the control group and will be calculated by dividing the probability of contracting an SSI in the intervention group by the control group=$\frac{SSIrateinterventiongroup}{SSIratecontrolgroup}$. The effect size will also be presented as an absolute risk difference=SSIrateinterventiongroup−SSIratecontrolgroup.

The primary outcome is a surrogate variable for SSI as it, due to the large sample size, is practically impossible to have all patients come back for outpatient visits and be visually inspected. To further validate the outcome, a medical record review will be performed in a second step on all individual patients with indication of SSI. Our expectations are that the choice and succeeding validation of this proxy variable can provide us with a reliable tool for investigating SSI’s in future projects.

The Swedish healthcare registers, especially the Prescribed Drug Register (PDR) and the Patient Register, will make sure that we get an almost complete (>99%) coverage of all relevant SSIs.

The secondary outcomes are: (1) withdrawal or other documented use of any antibiotics for 2 days or more after surgery during the first 30 postoperative days, (2) the number of days with antibiotics during the first 30 days, (3) same as (1) and (2) but up to 90 days after surgery and (d) death during the first 2 postoperative years

These analyses will also be performed with and without adjustment for preoperative antibiotic use 6 months prior to the surgery.

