### Sample size

The reoperation rate in Sweden due to infections within the first 2 years after surgery is 1.3%^3^ for primary total hip replacements (THRs). This does not include THRs in patients with fracture and other types of surgeries that are more susceptible to infections. We, therefore, assume that the SSI rate in our study population is 2%.^1–3^ Similarly, we know from other data that about 0.7% withdraw the antibiotics associated with the primary outcome within a 3-month period prior to surgery. To account for infections unrelated to surgery, we assume that the infection noise rate, that is, non-SSIs, is less than 2%.

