#### Multicentre power with ultra-clean air

Hospitals with ORs with ultra-clean air may be less susceptible to the effect with an already lower infection rate. Pre-study CFU measurements suggest that approximately 80% of the included ORs are ultra clean. If we assume that the infection rate is 2% or less, and that the effect size is reduced to 25% in an ultra-clean environment, we will need to recruit 22 630 patients in each group, that is, approximately 45 000 patients to attain a power of 80% with a significance level of 0.05. This will be our target population. We expect a very low drop-out rate/missing data in the study, estimated to be <1%. At the interim analysis, the p value will be set 10 times lower at 0.005, that is, if a statistically significant result between the groups is observed at 18 months, the study will be stopped. See figure 3 and online supplemental appendix 1 for details in R and explanation of the script for the sample size analysis.

10.1136/bmjopen-2020-047500.supp1Supplementary data

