## Methods: data collection, management and analysis

### Data collection methods

For the primary endpoint, the following codes will be used to detect if individual patients have contracted an SSI following surgery. If any of these codes indicate SSI, a chart review will be performed in a second step to verify the outcome:

From the Swedish PDR: withdrawal of antibiotics targeting *S. aureus* corresponding to a minimum amount of two defined daily dosages (an estimate provided by the registry for the expected daily dosage). The date of withdrawal will serve as an indicator of treatment start unless inpatient data are available with more granular information. The drug Anatomical Therapeutic Chemical (ATC) codes considered to target relevant bacteria are:J01CF05 (isoxazolylpenicillin).J01FF01 (clindamycin).J04AB02 (rifampicin).From The National Patient Registry: ICD trigger codes indicating postoperative infections:T793: posttraumatic wound infection, not elsewhere classifiedT814: infection following a procedure, not elsewhere classifiedT84[5-7]: infection and inflammatory reaction due to internal joint prosthesis, internal fixation device or other internal orthopaedic prosthetic devices, implants and graftsT874: infection of amputation stumpB9[5,6,8]: bacterial specificationL0[2-4]: cutaneous abscess, furuncle and carbuncle, and cellulitis.A[24]6: erysipeloid and erysipelasFrom the National Patient Registry: NOMESCO trigger codes indicating postoperative infections:Incision abscess: TN[A-H]05Surgeries due infections: N[A-H]S[0–4,9]9.Extremities wound revision: Q(CD)B05.Reoperation for infection: N[A-H]W69.Vacuum treatment: DQ023.

Both local and national registry data will be used according to availability. For the admission episodes with the code indicators, the admission date is the index date, that is, if an admission occurs after 91 days with a trigger code it will not be considered an indicator of a postoperative infection.

In-hospital information systems will supply information on: (1) patient ID, (2) date(s) of surgery, (3) surgery associated codes, including operated side, (4) OR and (5) in-hospital antibiotics

Both the surgical and medical data records will be retrieved depending on availability. Only centres that can provide the above data will be allowed to participate.

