### Statistical methods

The primary outcome is a binary variable where there are three groups. We will use logistic regression where the reference group is the placebo group, and the significance is related to the intervention group. The estimate for the mixed group is only for relating dose effect, that is, the group will not be pooled with either the placebo or the intervention group. Due to the randomisation, we do not intend to have any other covariates as confounders in the model. Similar methodology will be applied to the antibiotic’s binary outcome. The number of days with antibiotics will be modelled using a linear regression with the similar interpretation to above regarding predictors. Mortality will be modelled using a Cox proportional hazards model with time since surgery calculated as time to death, migration or 2 years. The Cox model will not contain any covariates due to the randomised study nature. The analysis will be performed by an epidemiologist/statistician in our team (MG) and will be performed as a per-protocol analysis.

We will handle confounding by including only the patient’s first surgical procedure. The randomisation process will handle other confounding such as confounding by selection. Procedural confounding will be handled by the external part who has done the randomisation procedure for each PAP device. Regarding dropouts, the healthcare registers and chart review done in the study will ensure a very low (<1%) drop-out rate. Individual patients can also request that they are excluded from the registers and thus from the study, but by experience, this is very rare and will also not affect our ability to analyse our primary and secondary endpoints.

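### The primary model omits prognostic covariates on confounding grounds alone, giving up a small amount of precision that procedure codes already collected could supply

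*Protocol article*

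**What the plan says.** The relevant statements are all in the protocol article.

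- **Statistical methods.** The primary analysis is specified thus: "We will use logistic regression where the reference group is the placebo group". It has three exposure groups and no other terms. Randomisation is given as the reason: "we do not intend to have any other covariates as confounders in the model". The Cox model for mortality is left without covariates for the same reason. Precision is not mentioned.
- **Outcomes.** The effect is defined as a relative risk, and "The effect size will also be presented as an absolute risk difference". Both are marginal measures. Directly after the list of secondary outcomes, which includes death, analyses are promised "with and without adjustment for preoperative antibiotic use 6 months prior to the surgery".
- **Sample size.** The assumed infection rate is raised above the hip-replacement figure because that figure is too narrow: "This does not include THRs in patients with fracture and other types of surgeries that are more susceptible to infections". The protocol therefore expects risk to differ by procedure.
- **Data collection methods.** Hospital systems supply "surgery associated codes, including operated side" for each patient, and a centre that cannot provide these data may not take part.
- **Allocation.** The unit switched on or off is a whole OR for 4, 6 or 8 weeks.

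**The concern.** Randomisation removes the need to adjust for confounding, but it does not make prognostic covariates useless. A covariate that predicts the outcome takes explained variation out of the error and corrects chance imbalance. Here allocation is by OR-period, so a run of higher-risk surgery in one OR falls wholly in one arm. OR terms remove stable differences between rooms. They do not remove shifts in case mix within one room from period to period, whereas procedure group partly does.

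The design aims only for 80% power, and the protocol names the large sample as its main limitation. Precision that needs no new data is therefore worth having, even if modest.

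There is also an inconsistency. The Outcomes section promises adjusted analyses after a list that includes death, while Statistical methods rules out covariates in the mortality model. Neither section says whether the adjusted analyses extend to the primary outcome.

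**Working it through.** **1. The plan's own sample size.** From Sample size and the multicentre power subsection: SSI 2%, unrelated infections up to 2%, 25% reduction, 80% power, significance level 0.05. Adding the unrelated infections to both arms gives 0.02 + 0.02 = 0.040 for control and 0.015 + 0.02 = 0.035 for intervention. With a two-sided test:

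n = [1.96 × √(2 × 0.0375 × 0.9625) + 0.8416 × √(0.04 × 0.96 + 0.035 × 0.965)]² / 0.005² = 22 663 per group

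The plan states 22 630, so the figure is reproduced to within 0.15%. Using 2.0% v 1.5% without the unrelated infections gives 10 795, which does not match. The plan's calculation therefore includes them, and any estimate of the gain must too. At 22 500 per group and with independent patients, power is 79.7%.

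**2. Gain on the risk-difference scale.** The documents give no number of ORs, cluster size, procedure risks or case-mix variation. Assumed:

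- 30 ORs × 41 periods × 37 patients = 45 510;
- two procedure groups with SSI risks of 1% and 4% (the ends of the incidence range in the Introduction), plus 2% unrelated infections in both, so 3% v 6% in total and a contrast d = 0.03;
- a high-risk share h from 1 + 3h = 2, so h = 1/3;
- a standard deviation s of that share between periods within an OR of 0.10, 0.15 or 0.20;
- a comparator that already has OR terms and cluster-robust errors.

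Formulae:

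- Outcome variance = 0.0375 × 0.9625 = 0.03609.
- R² = d² × h(1 − h) / 0.03609 = 0.0009 × 0.2222 / 0.03609 = 0.0055.
- ICC = d²s² / 0.03609, and design effect DE = 1 + 36 × ICC.
- Variance ratio, adjusted to unadjusted = (1 − R²) / DE.
- Power = Φ(0.005 / √(V × f) − 1.96), with V = 0.072175 / 22 500 and f = DE (unadjusted) or 1 − R² (adjusted).

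| s | ICC | DE | Ratio | Variance cut | Power unadjusted | Power adjusted | Gain (points) |
|---|---|---|---|---|---|---|---|
| 0.10 | 0.00025 | 1.009 | 0.986 | 1.4% | 79.4% | 79.9% | 0.6 |
| 0.15 | 0.00056 | 1.020 | 0.975 | 2.5% | 78.9% | 79.9% | 1.0 |
| 0.20 | 0.00100 | 1.036 | 0.960 | 4.0% | 78.3% | 79.9% | 1.6 |

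These use the control-arm contrast. If the 25% reduction applies in both procedure groups, the contrast in the intervention arm is 0.75 × 0.03 = 0.0225 and the average is 0.02625. The cuts then scale by about (0.02625 / 0.03)² = 0.77, to about 1.1%, 1.9% and 3.1%. The table is therefore towards the high side for these inputs.

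**3. The scale matters.** For independent patients, with a prognostic score of assumed strength (AUC 0.64 to 0.76, R² about 1 to 5%), the asymptotic variance of the logistic coefficient gives:

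- the standard error of the log odds ratio rises, by a factor of 1.005 to 1.024;
- the coefficient moves from −0.139 to between −0.140 and −0.146;
- power goes from 79.7% to between 80.1% and 81.5%.

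In a logistic model the gain is therefore in power, with no shorter interval for the log odds ratio. For the relative risk and risk difference defined under Outcomes, the gain in precision comes through standardised estimates.

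**The case against.** The strongest case against is that nothing here is an error. The unadjusted comparison is valid under randomisation, the text declines covariates only as confounders, and a separate analysis plan may add detail. That largely stands and limits the point to efficiency. What remains is that the article gives a positive reason for having no covariates, and that reason does not cover precision.

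A reader might infer more than the documents support:

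- **That the primary result is biased.** It is not biased by this omission.
- **That the loss is large.** Simulated total risks of 2% v 10% gave a variance cut of about 11%, or 45 000 × (1/0.893 − 1) ≈ 5 400 patients. But once the plan's 2% unrelated infections are subtracted, the low-risk group has no SSI at all. The same is true of 2% v 6% (a cut of 3 to 4%). Total risks of 2.6% v 8% gave 3 to 8%, but imply SSI of 0.6% v 6%, a tenfold contrast. Procedure type has little reason to predict unrelated infections, which are half of the assumed control-arm events.
- **That clustering of case mix makes this a major point.** With 40 patients per OR-period, R² of 1 to 5% and 5 to 10% of it lying between OR-periods, the design effect is 1.02 to 1.20 and unadjusted power 79% to 72%. Adjustment could recover part of that. But the documents give no ICC or cluster size, and the main defect there is that the model ignores the randomisation structure.
- **That pre-operative antibiotic use belongs in the primary model.** No gain has been shown. The Sample size section puts pre-operative use of the trigger drugs at about 0.7% over three months, and patients with antibiotics within two weeks of surgery are excluded.

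On timing, Data monitoring dates an interim analysis 17 April 2018, and allocations up to an interim are released. A grouping fixed before any release may no longer be possible, but one fixed before any further release is.

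**Conclusion.** The point holds as a minor, inexpensive improvement. The stated reason for an unadjusted primary model concerns confounding only. The protocol itself says that risk differs by type of surgery, and it collects the codes needed to adjust. The cost of not adjusting is roughly 1.5 to 4% of the variance of the risk difference, or about 0.5 to 1.5 power points. This rests on the assumed 1% v 4% SSI split, 37 patients per OR-period and a case-mix standard deviation of 10 to 20 points. None of these is a planning figure in the documents, and different values would move the result. The mismatch between Outcomes and Statistical methods on adjusted analyses needs resolving whatever the size of the gain.

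**What to change.** In Statistical methods:

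1. Replace the sentence that rests on randomisation with a pre-specified primary model containing a few procedure groups derived from the codes already extracted (for example primary arthroplasty, fracture surgery, spine, other), alongside terms for the randomisation structure.
2. From that model, report the standardised (marginal) relative risk and risk difference that Outcomes defines, with standard errors that allow for OR-period clustering. A covariate-adjusted odds ratio alone would be a conditional measure and would not match the stated effect measures.
3. Fix the code-to-group list before any further allocation is released to the analysts.
4. Report the unadjusted estimate as a sensitivity analysis.
5. State whether the analyses with and without adjustment for pre-operative antibiotics cover the primary outcome and the mortality model, and make the two sections agree. Pre-operative antibiotic use may be added to the primary model, but it should not be justified by a precision gain that has not been shown.

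The cost is one paragraph, a fixed grouping table and a little more analysis work. No new data are needed.

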### Intervention

At each hospital, all ORs that perform surgery on orthopaedic patients will be equipped with three^3^ PAP systems each. The groups are defined as: intervention group: those operated where the PAP device has been turned on for at least 2 days prior to index surgery; control group: those where the PAP device has been turned off for at least 2 days prior to index surgery; and mixed group: those receiving surgeries in ORs within 2 days after the PAP device switches status. In the analysis we will also subgroup the study subjects according to measurements prior to study start into regular ORs (≥10 CFU/m^3^) and ultra-clean ORs (<10 CFU/m^3^).

PAP device status and function will be monitored continuously during the inclusion period through standardised manual controls every 3 months, and also at the end of the inclusion period by validating PAP device status retrospectively through memory card recordings in each device.

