## Methods: an assignment of interventions

### Allocation

The three PAP devices in each OR will synchronically be randomised in periods of 4 weeks, 6 weeks or 8 weeks to either have the system ‘on’ or ‘off’. The switch will always occur midnight Friday in order to limit the patients exposed to partial effect during the first 2 days after switching status. The system can be programmed to be active (ie, plasma chamber eradicating bacteria) at any given timeframe. The manufacturer of the PAP devices will prepare the randomisation allocation and automatic execution of it. The randomisation sequence is at minimum 8 years long and will be submitted to a third, independent party, responsible for keeping the allocation secret until interim analyses or study end. At the interim analyses, only allocations up to that date will be released.

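### Per-protocol is the only stated analysis and arms are defined by device status, so malfunctions could weaken the randomised comparison; analysis by allocated schedule should be primary

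*Protocol article*

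**What the plan says.** The Statistical methods section plans a logistic regression with three groups (intervention, placebo, mixed). It includes no covariates, on the ground that the trial is randomised, and says the analysis "will be performed as a per-protocol analysis". No intention-to-treat or as-allocated analysis is named anywhere in the article.

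The Intervention section defines the intervention group as "those operated where the PAP device has been turned on for at least 2 days prior to index surgery" and the control group as "those where the PAP device has been turned off for at least 2 days prior to index surgery". Patients operated on within 2 days after a switch form the mixed group, and "the group will not be pooled with either the placebo or the intervention group". Device status is followed by "standardised manual controls every 3 months" and, after inclusion ends, by "validating PAP device status retrospectively through memory card recordings in each device".

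The Allocation section randomises each operating room (OR) in periods of 4, 6 or 8 weeks, executed automatically. A third party holds the sequence and releases it at the interim analysis (up to that date) and at study end.

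**The concern.** This is a superiority question, and randomisation justifies leaving out covariates only for groups formed by the allocation. Here the groups are described by device state, and the single analysis label is per-protocol. If what the device actually did decides who is analysed and in which arm, the compared sets are no longer purely those that randomisation created.

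A failed plasma chamber changes status only in a period allocated on; the same failure in an off period changes nothing. Exclusions from that cause would fall on one arm, and on particular ORs and dates. Manual checks are 3 months apart, longer than any allocation period, so a fault could run through a whole period unnoticed until the cards are read. The planned model has no OR, centre or period term to absorb a resulting imbalance. At stake is a spurious shift in the primary risk ratio, in either direction.

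**Working it through.** **1. The plan's own figure.** Inputs from the Sample size section and its subsection on ultra-clean air: surgical site infection rate 2%, unrelated infections below 2% (taken as 2%), 25% reduction, 80% power, significance level 0.05 (taken as two-sided). The trigger rates are then 2% + 2% = 4.0% in controls and 1.5% + 2% = 3.5% with the device on.

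n per arm = [1.96·√(2·0.0375·0.9625) + 0.8416·√(0.04·0.96 + 0.035·0.965)]² / 0.005² = 22,663, against 22,630 stated. The plan's figure reproduces and contains no allowance for device failure. The design risk ratio (RR) on the trigger endpoint is 3.5/4.0 = 0.875.

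**2. Shift under a device with no effect.** Let f be the share of on-patients whose devices were in fact off, and r the event risk of those patients relative to the average. The article gives neither, so both are assumptions. Only chamber failures in on periods are modelled.

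- Excluded: RR = (1 − fr)/(1 − f)
- Moved to control: RR = [(1 − fr)/(1 − f)] / [(1 + fr)/(1 + f)]

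| f | r | Excluded | Moved to control |
|---|---|---|---|
| 5% | 1.5 | 0.925/0.95 = 0.974 | 0.974/(1.075/1.05) = 0.951 |
| 10% | 1.5 | 0.85/0.90 = 0.944 | 0.944/(1.15/1.10) = 0.903 |
| 5% | 0.67 | 0.9665/0.95 = 1.017 | 1.017/(1.0335/1.05) = 1.034 |
| 10% | 0.67 | 0.933/0.90 = 1.037 | 1.037/(1.067/1.10) = 1.069 |
| any | 1 | 1 | 1 |

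None of these values reaches 0.875. At r = 1.5, solving the formulas for RR = 0.875 needs f = 20% under exclusion or about 13% under reclassification.

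**3. Rough effect on the test.** Here r is set against other OR time instead of the average, so the RR under exclusion is 1/(1 + f(r − 1)). With 22,500 per arm, a 4% overall rate, r = 1.5 and no clustering, the false-positive rate for f = 5% and 10% is 8.2% and 17% under exclusion (RR 0.976 and 0.952). It is 17% and 46% if patients are moved (RR 0.955 and 0.917). The nominal level is 5%.

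**4. Price of analysing by schedule.** Keeping failures in, the on-arm rate is 0.035 + 0.005f.

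| f | On-arm rate | Power by schedule, 22,500 per arm | n per arm for 80% | Power if failures are excluded |
|---|---|---|---|---|
| 0 | 3.50% | 79.7% | 22,663 | 79.7% |
| 2% | 3.51% | 78.1% | 23,628 | 79.3% |
| 5% | 3.525% | 75.4% | 25,192 | 78.7% |
| 10% | 3.55% | 70.7% | 28,158 | 77.5% |

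**The case against.** The strongest defence is that the article does not say what happens to patients in a malfunctioning on period. A reader might infer that they are dropped or moved to control. The text says neither: turned on or off could mean the programmed state, and the cards are said to validate status, not to reassign patients. Because the sequence is released at the interim while the cards are read only after inclusion ends, the interim comparison may well rest on the schedule. This stands, and it is why the point is conditional.

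A reader might also infer that the randomised comparison is lost. The documents do not support that. Switching is automatic and staff, surgeons and patients are blinded, so deviation driven by prognosis, the usual per-protocol hazard, is unlikely. With no failures the two analyses coincide outside the mixed group, and failures unrelated to risk cost precision without bias.

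Nor is the problem strictly one-sided. A switching fault could leave a device running in an off period, and with three devices per OR one failure need not change the room's status.

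Finally, it is tempting to say that the choice could create an effect of the size sought. At 5-10% affected and 1.5 times the risk it does not.

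The argument that all this belongs in an unseen analysis plan stands only in part. Handling of malfunctions may be detailed there, but per-protocol as the analysis is a choice that the article states. If the label was meant only to set aside the mixed group, the article does not say so. The mixed group is not in question, since its window follows the scheduled switches in both directions.

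**Conclusion.** The concern holds in conditional form and should be fixed, but it is not a fatal flaw. The article fixes per-protocol as the only stated analysis of a randomised superiority trial, describes the arms by device status, and makes no commitment to the allocated schedule. If malfunctions occur and observed status decides membership, the unadjusted comparison is no longer fully protected by randomisation.

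The size depends on two quantities that the article does not give: how often devices failed, and whether failures fell in ORs or periods of different risk. The protocol itself expects risk to differ between ORs, since it says that ultra-clean rooms may already have a lower infection rate. It gives no sign that failures follow that difference. Over the assumed range the shift is a few per cent to about 10% of the risk ratio, in either direction, against a design reduction of 12.5% on the trigger endpoint.

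**What to change.** Replace the per-protocol sentence with a primary analysis by allocated schedule: each patient counts as on or off as scheduled for that OR on the surgery date, malfunctions are kept in, and the mixed window is defined from the scheduled switch. Report the memory-card per-protocol analysis as a sensitivity analysis, with exclusions and reclassifications counted by allocated arm.

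The work is one changed sentence and one further analysis run. The third party already holds the sequence, so the analysis is possible at the interim as well as at the end. The real cost is dilution if failures were common. It is small at 2% failed on-time; at 10%, power by schedule is about 71%, against about 78% if failures are excluded. The failure rate should therefore be reported alongside the result.
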